### Safety Analysis

The safety analysis will be based on the safety population. The assessment of safety will be based mainly on the frequency of adverse events or serious adverse events the acute and late toxicities and on the number of laboratory values that fall outside of pre-determined ranges and/or show prominent worsening. Furthermore, the most common AEs (those occurring in at least 10% of the treatment group) will be determined. Any other information collected (e.g. severity or relatedness to study drug) will be listed as appropriate. Incidence rates and exact Pearson-Clopper 95% confidence bounds [27] of AE will be summarized.

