**Methods/design:**

This clinical study is a prospective randomised phase III trial. The trial will be carried out at Heidelberger Ionenstrahl-Therapie centre (HIT) and is a monocentric study.

Patients with skull base chordoma will be randomised to either proton or carbon ion radiation therapy. As a standard, patients will undergo non-invasive, rigid immobilization and target volume delineation will be carried out based on CT and MRI data. The biologically isoeffective target dose to the PTV in carbon ion treatment (accelerated dose) will be 63 Gy E ± 5% and 72 Gy E ± 5% (standard dose) in proton therapy respectively. Local-progression free survival (LPFS) will be analysed as primary end point. Toxicity and overall survival are the secondary end points. Additional examined parameters are patterns of recurrence, prognostic factors and plan quality analysis.

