## Organization, Workflow and Follow-up

Patient data will be collected and documented pseudonymously using electronic data processing (e.g. patient initials, date of birth and study number) at the study office at HIT. Table 3 presents a brief workflow.

**Table 3 T3:** Workflow time table

Approval of ethics committee
↓
Diagnosis of chordoma of the skull base and completion of pre-radiation treatment examinations (biopsy, operation, staging)
↓
Informed consent of the patient and patient registration by the study office at HIT
↓
Stratification and Randomisation
↓
Arm A: carbon ion RT (63 Gy E ± 5%, fractionation 4-6 × 3.0 Gy E) Arm B: proton RT (72 Gy E ± 5%, fractionation 4-6 × 2.0 Gy E)
↓
Treatment planning for particle therapy
↓
Particle therapy
↓
Follow-up

After randomisation the study number will be assigned.

The following study data will be collected at the study office at HIT:

1. Medical reports including pathology reports and results of staging and additional pre-treatment examinations

2. Documentation of RT (dose distributions and DVH) and position checks

3. Prescribed total target dose and fraction doses, treatment interruptions >4 days

4. Toxicity data

5. Follow-up forms

6. Trial-related documentation including severe AE (CTCAE Grad ≥ 3) will be reported immediately to the study office and the principal investigator of the study

7. The date of local recurrence (MRT or CT - morphological tumour progress in the former irradiated region), distant metastases or death of the patient will be reported and documented.

Local recurrences will be confirmed radiologically and histologically whenever possible. At least two medical doctors (radiation oncologist and/or radiologist) will be required to judge of the recurrence or toxicity.

Every patient is followed for LPFS and trial-related AEs for a time period of 8 years. Furthermore, patients will be followed for survival and locoregional recurrences for a time period of 8 years after completion of the irradiation.

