The first and the second follow-up examination will be performed 4-6 weeks and 3 months after completion of RT (follow-up 1 and 2). Follow-up examinations will then be scheduled after 6 months (follow-up 3), 9-12 months (follow-up 4), and then once a year for further 6 years (follow-up 5, 6 and 7). Additional visits will be scheduled as necessary. Acute toxicity is assessed at least weekly during RT and documented at the end of the RT series, 6 weeks after completion of RT and 3 months after RT. Late toxicity will be documented in regular intervals of 6 or 12 months during the observation period. All the patients will be observed for radiation specific acute and late AEs for the time of at least 8 years after irradiation. The maximum grade of toxicity will be determined for each patient.

The Common Terminology Criteria for Adverse Events V4.0 (CTCAE V.4.0) will be used to grade acute toxicity from radiation therapy. The criteria are relevant from the 8th irradiation day until day 90, i.e. until the 1st follow-up visit. Thereafter, the RTOG/EORTC Criteria of Late Effects will be utilized. All acute radiation effects will be documented on an Acute Radiation Effect-Form. In addition, the AE-Form and/or SAE-Form will be filled out. RTOG/EORTC Late Morbidity Scoring Scheme will be used to grade toxicity from radiation therapy occurring later than 90 days after its start, i.e. beyond the 1st follow-up visit. All late radiation effects will be documented on a Late Radiation Effect-Form. In addition, an AE-Form and/or SAE-Form will be filled out, if late radiation effects appear.

The follow-up examinations contain:

- Medical history

- Clinical examination

- MRI or CT of the head

- Documentation of acute side effects/AE (CTCAE V.4.0) up to 90 days after RT

- Documentation of late side effects/AE (RTOG/EORTC) after 90 days after RT

- Reporting/documentation of acute grade 3 or 4 toxicity or grade 3, 4 or 5 late effects.

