### Sample Size Determination

The sample size is calculated on the basis of the following assumptions:

• LPFS rate 5 years after radiation therapy of 70% 1) for proton therapy, hazard λ_1 _= 0.0713, and 80% for carbon ion therapy, hazard λ_2 _= 0.0446 (hazard ratio = 1.599).

• Recruitment period of 5 years, with constant accrual rate of 20% patients per year and a follow-up time of 8 years.

• One interim analysis according to a group sequential design with two stages.

Formula of Schoenfeld [20,21] used for the calculation of the number of accumulated events. For a two-sided logrank test with an overall two-sided significance level of 0.05 (including interim and final analyses) and power of 0.80, 143 events are required. The critical values and the test characteristics of the group sequential test design were calculated for an O'Brien and Fleming type alpha spending function. The computation assumes equal allocation to the two groups (n_2_/n_1 _= 1). Assuming an accrual time of 5 and a maximum observation time of 13 years a total of 319 patients is expected to yield the necessary number of events if the accrual rate is constant. Under these assumptions, the time point of the interim analysis should be 7 years after the first patient is entered. The ADDPLAN, Version 4.0 calculator was used for the sample size estimation. With the assumption that approximately 7% of the patients will be lost to follow-up a total of 344 patients will be needed to accumulate 143 events.

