### Interim Analysis

There is one planned interim analysis. The purpose for performing the interim analysis is to support a possible early detection of the superior therapy. In case of reaching a critical value of 2.9626 in the interim analysis the underlying therapy should neither be used for any further patients treated within the study nor for any patients outside of the study.

The interim analysis will be performed as soon as 50% of the expected events have occurred. Assuming that rate of recruitment proceeds at the rate estimated for this study the time of the interim analysis will be approximately 7 years after the first patient is entered. This time point is after the end of recruitment. For this reason the interim analysis does not have the goal to stop the study early and should not define a critical value of early stopping for futility. Independent of the result of the interim analysis the study should continue as planned with the recruited and already treated patients.

Interim statistical hypothesis tests will be performed only for the primary efficacy endpoint, LPFS. The log-rank test identical to the primary analysis will be performed at the scheduled interim analysis and compared to group sequential boundary based on the current information time. The LPFS curve estimated by the method of Kaplan-Meier will be summarized for each treatment group. The hazard ratio will also be estimated. The interim safety report will review all aspects of the data collected for each subject. Other important additional factors that reflect the integrity of the protocol will be addressed in the interim report.

A group sequential design with an O'Brien and Fleming alpha spending function is used to control the type I error. The nominal one-sided significance level for the interim analysis determined by using the O'Brien-Fleming stopping rule is 0.0015.

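### Late toxicity is planned as a crude proportion with exact binomial limits, so it refers to no defined time point and counts patients lost early as free of late effects

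*Protocol article*

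**What the plan says.** The protocol article's abstract makes toxicity a headline outcome: "Toxicity and overall survival are the secondary end points". The Safety Analysis section puts late effects under the same frequency-based summary as acute ones: "The assessment of safety will be based mainly on the frequency of adverse events or serious adverse events the acute and late toxicities". It names the method: "Incidence rates and exact Pearson-Clopper 95% confidence bounds [27] of AE will be summarized". Under Organization, Workflow and Follow-up, toxicity is reduced to one value per patient with no time attached: "The maximum grade of toxicity will be determined for each patient".

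The length of observation is described in several ways:
- Follow-up section: "Every patient is followed for LPFS and trial-related AEs for a time period of 8 years", and also "All the patients will be observed for radiation specific acute and late AEs for the time of at least 8 years after irradiation".
- Sample Size Determination: "Assuming an accrual time of 5 and a maximum observation time of 13 years", with about 7% of patients expected to be lost.
- Interim Analysis: one look about 7 years after the first patient enters, when "The interim safety report will review all aspects of the data collected for each subject".

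By contrast, Kaplan-Meier and log-rank methods are named for LPFS, overall survival, progression-free survival and metastasis-free survival. The censoring rule under Analysis Populations covers time-to-event data only. No time-to-event method is named for late toxicity.

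**The concern.** Clopper-Pearson limits belong to a binomial count: patients with an event out of patients treated. Such a proportion has a clear meaning when everyone is observed for the same period, or until death within that period. That is nearly true of acute toxicity and not of late effects. A patient lost at year 2 enters as a full non-event. A patient observed for 13 years has five more years in which to become an event than one observed for 8. The result is an average over whatever follow-up happened to accrue, so it cannot be read as a 5-year or an 8-year risk.

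Late toxicity is half of the risk-benefit comparison of the two particles, and the protocol's early-termination criteria rest largely on adverse events. A crude figure that is low at the interim and high at the end, for the same underlying hazard, is a poor basis for either.

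**Working it through.** **Step 1. Follow-up pattern, from the plan's own sample size.**
- Hazards: −ln(0.70)/5 = 0.0713 and −ln(0.80)/5 = 0.0446, ratio 1.598.
- Schoenfeld: 4 × (1.960 + 0.842)² / (ln 1.598)² = 142.7, so 143 events, as stated.
- Event probability with uniform accrual over 5 years and analysis at 13 years: 1 − [exp(−8λ) − exp(−13λ)]/(5λ) = 0.5247 (protons) and 0.3728 (carbon), mean 0.4487.
- 143/0.4487 = 318.7, so 319. 319/0.93 = 343.01, so 344. Both as stated.
- With a fixed 8 years per patient the mean event probability is 0.3676, and 143/0.3676 = 389 patients.

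The stated 319 therefore implies 8 to 13 years of observation for LPFS. At year 7, after 5 years of accrual, observation runs from 2 to 7 years.

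**Step 2. Inputs for late toxicity.** The protocol gives no late-toxicity risk, so these are assumptions:
- Net 5-year risk of 10% (range 5 to 20%), with the same hazard h in both arms.
- Latency L of 0 or 1.5 years, so h = −ln(0.90)/5 = 0.0211 or −ln(0.90)/3.5 = 0.0301.
- Death hazard d from the 5-year survival figures in the Background, used only as illustration: 88.5% in the earlier carbon series gives −ln(0.885)/5 = 0.0244. 79% in a 33-patient proton series at another centre gives −ln(0.79)/5 = 0.0471.
- Toxicity independent of death, constant hazards, no losses (see step 4).

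**Step 3. Crude rate against cumulative incidence.** With death competing,

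CIF(t) = exp(−dL) × h/(h+d) × {1 − exp[−(h+d)(t−L)]}.

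Example (carbon, L = 0, t = 8): (0.0211/0.0455) × [1 − exp(−0.364)] = 0.463 × 0.305 = 14.1%. The expected crude rate is CIF averaged over uniform follow-up of 2 to 7 or 8 to 13 years.

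| | Carbon, L=0 | Carbon, L=1.5 | Proton, L=0 | Proton, L=1.5 |
|---|---|---|---|---|
| Crude, interim | 8.49% | 7.89% | 8.05% | 7.33% |
| CIF at 5 years | 9.42% | 9.25% | 8.93% | 8.60% |
| Crude, end | 17.53% | 20.54% | 15.72% | 18.08% |
| CIF at 8 years | 14.13% | 15.88% | 12.99% | 14.33% |

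Within the carbon arm the final crude figure exceeds the 8-year cumulative incidence by 3.4 points (L = 0) or 4.7 points (L = 1.5).

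**Step 4. Losses.** As a bound, suppose that all 7% are lost before any late effect can be seen. The final carbon figures become 17.5 × 0.93 = 16.3% and 20.5 × 0.93 = 19.1%. These are still above the 8-year values, and they are now too low for the follow-up that they cover.

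**Step 5. Between arms.**
- Equal mortality and follow-up: the difference is zero at any follow-up length.
- Survival of 88.5% against 79%: 17.53 − 15.72 = 1.8 points (L = 0) or 20.54 − 18.08 = 2.5 points (L = 1.5), at identical late-effect hazards. Over assumed risks of 5 to 20% the range is about 1 to 4.4 points.
- Scale: at 344/2 = 172 per arm, the standard error √[p₁(1−p₁)/172 + p₂(1−p₂)/172] is 4.0 to 4.3 points at the 10% risk. The excess is about half a standard error, and it stays below one over the whole range.

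**Step 6. What each remedy removes.** At 8 years the cumulative incidences still differ at equal hazards, by 14.13 − 12.99 = 1.14 or 15.88 − 14.33 = 1.55 points. That is about 60% of the crude excess. Only the ratio of cause-specific hazards, h/h = 1.00 here, is free of the mortality difference.

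**The case against.** A reader might infer that the crude method does distort the comparison against carbon ions. The documents do not support that. The visit schedule and the follow-up period are common to both arms. Observation for radiation-specific adverse events continues after recurrence or metastasis. The 7% loss is not split by arm. The planned effect is on LPFS, not on mortality. The two survival figures come from unrelated series, and their hazard ratio, 0.0471/0.0244 = 1.93, exceeds the 1.599 assumed for LPFS itself. This part of the objection stands in full, so any arm bias is conditional.

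It is also fair that the Safety Analysis section is descriptive and names no test of late effects between arms, and that interim tests are confined to LPFS. However, the secondary-analysis section says that results generally come with test statistics and p-values.

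If follow-up were complete to exactly 8 years, as one sentence of the follow-up section can be read, the crude proportion would be a valid 8-year cumulative incidence with death competing, and the final discrepancy in step 3 would vanish. The wording elsewhere (at least 8 years, up to 13, 7% lost) does not secure this, and the interim figure would still cover mixed follow-up.

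Last, crude incidence with exact limits is a conventional safety table, and an unseen analysis plan may add to it. That lowers the severity. It does not remove the point, because the article itself names the method and applies it to late effects.

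**Conclusion.** The point holds as a minor one. The named summary is a crude binomial proportion that ignores time at risk. For late effects it refers to no defined time and counts early losses as event-free. With an assumed 10% net 5-year risk it lies about 0.9 to 1.4 points below the 5-year cumulative incidence at the interim. At the end it lies about 3.4 to 4.7 points above the 8-year value in the carbon arm. The final figures rest on 8 to 13 years of observation for toxicity, constant hazards after any latency, and independence of toxicity and death.

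Bias between arms is not established. It is zero with equal mortality and follow-up. It is about 2 points against the longer-surviving arm under the illustrative 88.5% and 79%, which is less than the sampling error of the difference.

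**What to change.** For late effects (after day 90), report the Aalen-Johansen cumulative incidence of first grade 3 or higher toxicity at fixed times, for example 2, 5 and 8 years. Give 95% confidence intervals, treat death as a competing event, censor at the last toxicity assessment, and state the time origin. Use the same estimator in the interim safety report, at the times that follow-up then supports. This repairs the horizon and the losses.

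For any comparison of arms, add the cause-specific hazard ratio with its 95% confidence interval, because cumulative incidence alone still carries the effect of unequal mortality.

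Keep crude rates with Clopper-Pearson bounds for acute toxicity, where follow-up is nearly complete.

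The cost is a few lines in the analysis plan and a little programming. Death dates and scheduled late-toxicity assessments are already to be documented. Where no onset date is recorded, the date of the first visit at which the effect is graded can serve. No change to sample size or visits is needed.

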### Interim Analysis

There is one planned interim analysis. The purpose for performing the interim analysis is to support a possible early detection of the superior therapy. In case of reaching a critical value of 2.9626 in the interim analysis the underlying therapy should neither be used for any further patients treated within the study nor for any patients outside of the study.

The interim analysis will be performed as soon as 50% of the expected events have occurred. Assuming that rate of recruitment proceeds at the rate estimated for this study the time of the interim analysis will be approximately 7 years after the first patient is entered. This time point is after the end of recruitment. For this reason the interim analysis does not have the goal to stop the study early and should not define a critical value of early stopping for futility. Independent of the result of the interim analysis the study should continue as planned with the recruited and already treated patients.

Interim statistical hypothesis tests will be performed only for the primary efficacy endpoint, LPFS. The log-rank test identical to the primary analysis will be performed at the scheduled interim analysis and compared to group sequential boundary based on the current information time. The LPFS curve estimated by the method of Kaplan-Meier will be summarized for each treatment group. The hazard ratio will also be estimated. The interim safety report will review all aspects of the data collected for each subject. Other important additional factors that reflect the integrity of the protocol will be addressed in the interim report.

A group sequential design with an O'Brien and Fleming alpha spending function is used to control the type I error. The nominal one-sided significance level for the interim analysis determined by using the O'Brien-Fleming stopping rule is 0.0015.

## Ethical and legal aspects

The study plan has been submitted to the ethics committee of the Medical faculty Heidelberg for approval. The written approval by the ethics committee has been already obtained. Additionally, we received the positive vote of Bundesamt für Strahlenschutz for this study.

Prior to initiation of the treatment, patients will be informed about the goals of the trial in a conversation. Potential advantages and treatment related risks will be discussed with the patient. A written consent will be obtained and documented. The patient will be informed about the possibility to withdraw his agreement to participate in the study at any time without giving reasons. The responsible physician will inform the patient in his own language if possible and keep a record of this in the patient chart. The informed consent form will be signed. In case of cancellation the patient will be offered standard therapy.

The coordinating investigator has to subscribe to an insurance policy covering, in its terms and provisions, its legal liability for injuries caused to participating persons and arising out of this research performed strictly in accordance with the scientific protocol as well as with applicable law and professional standards.

Any impairment of health which might occur in consequence of trial participation must be notified to the insurance company. The subject is responsible for notification. The insured person will agree with all appropriate measures serving for clarification of the cause and the extent of damage as well as the reduction of damage.

During the conduct of the trial, the subject must not undergo other clinical treatment except for cases of emergency. The subject is bound to inform the investigator immediately about any adverse events and additional drugs taken. The terms and conditions of the insurance will be handed out to the subject on request.

The insurance company has to be informed about all amendments that could affect subjects' safety.

## Discussion

This study is designed as a prospective monocentric randomised phase III trial. The trial will be carried out at HIT centre. Proton therapy is the gold standard in the treatment of skull base chordomas. However, high-LET beams such as carbon ions theoretically offer biologic advantages by enhanced biologic effectiveness in slow-growing tumours. Up until now it was impossible to compare two different particle therapies, i.e. proton and carbon ion therapy directly with each other at the same institution. The aim of this study is to find out, whether the biological advantages of carbon ion therapy mentioned above can also be clinically confirmed.
